### 2.7. Interventions

#### 2.7.1. Lifestyle Modification

Both groups of patients get lifestyle intervention, with the following suggested living habits [31]: all individuals weighing 113.6 kg (250 lb.) will be provided a diet of 1200 to 1499 kcal/day consisting of standard foods with roughly 20% to 35% kcal from fat, 15% to 20% kcal from protein, and the remaining from carbohydrate. Those weighing 113.6 kg will be prescribed a diet of 1500 to 1800 kcal/day. Meanwhile, all participants will be instructed to keep a daily food and calorie diary, and they will be instructed to engage in low-to-moderate intensity physical activities such as jogging and walking for at least 5 days per week and for at least 210 minutes per week, preferably 270 minutes per week.

All patients will be required to keep a diet and exercise diary at least 4 days per week. The intervention time for lifestyle intervention includes a 12-week treatment phase and a 12-week follow-up period.

#### 2.7.2. “Moxibustion for Harmonization of Yin and Yang” Group

Shenque (RN8) and Mingmen (DU4) will be chosen as acupoints (Figure 2). The acupoints are located in accordance with the national GB/T 12346–2006 acupoints standard [32]. Each treatment lasts 60 minutes once a week and alternates between “Wenyang Yishen moxibustion” and “Peiyuan Guben moxibustion.” For a total of 12 weeks, each patient received “WenYang Yishen moxibustion” followed by “Peiyuan Guben moxibustion.” The width and length of the patient's moxibustion site are measured using the same body measurement method before performing “Wenyang Yishen moxibustion.” We take about 700 g of fresh ground ginger with moderate dryness and wetness and shape it into a round cake with a diameter of about 20 cm and a thickness of about 2.5 cm on a sterile towel. We light 25 g of moxa with a diameter of about 18 cm on top of the ginger. When the bottom temperature reaches approximately 37°, the moxibustion materials can be applied to the patient's waist for treatment. The temperature should be kept between 43 and 45°, depending on the patient's tolerance. It is preferable to add the moxa after about 10 minutes of burning. When moxibustion occurs, there is a slight red burning heat in the patient's partial skin. Moxibustion takes 60 minutes. The operation of “Peiyuan Guben moxibustion” is the same as that of “WenYang Yishen moxibustion,” which is centered on Shenque. Moxa is selected from folium *artemisia argyi* from Qichun County, Hubei. We slice the fresh ginger and put it into a ginger grinder to crush it to make about 1 mm minced ginger. We take out the minced ginger and squeeze out the excess water to keep the ginger mud soft and moist. The humidity is controlled at 80–90% (measuring with a moisture tester). The prepared grated ginger is stored in a refrigerator at 4°C and heated in a microwave oven on medium-high heat for 5 minutes before applying moxibustion. During the moxibustion process, a digital thermometer will be placed between the sterile towel and the acupoint to control the moxibustion temperature.

#### 2.7.3. Gentle Moxibustion Group

In this group, Zhongwan (RN12), Guanyuan (RN4), and Sanyinjiao (SP6) will be selected (Figure 3). In order to keep the local skin's surface temperature at 45°C ± 2°C for 20 minutes, a lit moxa stick (1.5 cm diameter moxa cone grown in Qichun County, Hubei, China) will be placed 2–3 cm away from the skin. For 12 weeks straight, a gentle moxibustion procedure will be performed every other day, three times per week. During the menstrual cycle, the treatment will be postponed.

### 2.8. Outcome Measurements

During the screening period, all subjects will fill out a questionnaire about demographic data such as gender, age, nationality, education level, occupation, marital status, height, and weight, as well as disease situations such as time and duration. Before randomization, serum follicular production hormone (FSH) levels will be measured and analyzed. Before treatment (screening period, first visit), after treatment (4th week, 8th week, and 12th week), and at follow-up (18th week and 24th week), each participant will receive a clinical assessment of primary and secondary outcome measurements. If both of the participants' menopausal obesity meet the inclusion criteria, the menopausal obesity with the more severe symptoms will be evaluated.  Figure 4 depicts the timetable for this study.

#### 2.8.1. Primary Outcome Measurement

Since waist circumference is the easiest and most practical indicator to quantify obesity; evaluations will be done at weeks 0, 4, 8, 12, 18, and 24 to compare the rate of waistline reduction with the baseline. The correct method for waist circumference is to check the horizontal length of the huckle center or the lowest point of the ribs and the middle line of the outer horizontal line of the iliac crest. In order to avoid the errors generated during the measurement process, the test is measured by a professional training doctor.

#### 2.8.2. Secondary Outcome Measurement

Obesity-related indicators: weight (WG), body mass index (BMI), hip circumference (HC), waist-hip-ratio (WHR), and body fat percentage (F%) will be evaluated by Omron somatic fat scalea (HBF-219T) at weeks 0, 4, 8, 12, 18, and 24.The Traditional Chinese Medicine clinical syndrome: the criteria for determining a diagnosis will be the TCM clinical syndrome scores. According to the 1997 5th National Obesity Research Conference's revisions to the diagnostic and treatment assessment criteria for simple obesity, lower scores indicate better physical conditions. The aggregate score runs from 0 to 30, and outcomes will be evaluated at weeks 0, 12, 18, and 24.The Impact of Weight on Quality of Life Questionnaire (IWQOL-Lite): patients' levels of life quality improvement is measured using the IWQOL-Lite scale, and there is a significant negative correlation between this scale and single overall life satisfaction. The total score runs from 31 to 155, with lower numbers indicating a higher quality of life, and outcomes will be evaluated at weeks 0, 12, and 24.The modified Kupperman score before and after treatment: the clinical symptoms of menopause are assessed using the modified Kupperman score. The total score runs from 0 to 63, with lower scores reflecting the lighter the patient's clinical symptoms; outcomes will be evaluated at weeks 0, 12, and 24.The MOS Item Short from Health Survey (SF-36) scale: a widely accepted health-related quality of life assessment is the SF-36. Higher scores indicate greater living quality. The total score goes from 40 to 147; outcomes will be evaluated at weeks 0, 12, and 24.Blood lipid-related indicators: low-density lipoprotein (LDL-C), high-density lipoprotein (HDL-C), cholesterol (TC), and triglyceride (TG) will be assessed at weeks 0 and 12, and the variation of the indicator is compared to baseline.Estrogen-related indicators include estradiol (E2), and serum follicles to form hormone (FSH). If the patient still has menstruation when the blood test is taken, the test is performed on the 2nd or 3rd day and the corresponding treatment time is delayed. The change value of this indicator is compared to baseline; outcomes will be evaluated at weeks 0 and 12.Health economics evaluation adopts cost-effective analysis, expressed in cost-effectiveness (COST/EFFECTIVESS, C/E).

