The Study of Women's Health Across the Nations (SWAN) [22], an observational cohort of menopausal female followed for over a decade, have suggested that after the onset of menopause, due to estrogen loss, women often continue to have bone loss, disrupted energy balance, and reduced physical activity and further accrue visceral fat, resulting in obesity [23]. Modern studies have shown that [24, 25] moxibustion can improve immunoglobulin and reduce proinflammatory cytokines and promote energy metabolism. It also has the effect of regulating nerves, anti-inflammatory properties, enhanced immunity, and accelerated metabolism.

Therefore, this multicenter randomized controlled research is on the variations in effectiveness between the two moxibustion prescriptions for treating menopausal obesity by assessing the safety, efficacy, and health economic evaluation of the “moxibustion for harmonization of Yin and Yang” compared to the gentle moxibustion, in order to increase the therapeutic impact and give high-quality evidence-based evidence for a better choice of moxibustion prescription.

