## 2. Methods and Design

### 2.1. Objectives

This study aims to (1) assess the effectiveness and security of moxibustion in the treatment of menopausal obesity; (2) compare the safety, efficacy, and health economic evaluation of different moxibustion methods for treating menopausal obesity, so as to optimize the prescription of moxibustion; and (3) investigate the effect of moxibustion in ameliorating the metabolism and relieving symptoms of menopause.

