### 2.2. Study Design

This will be a multicenter, randomized, controlled, two-arm clinical trial, where 216 participants will be randomized at a ratio of 1 : 1 to two groups (108 participants per group). There are six academic hospitals in China where this study will be carried out: Hubei Provincial Hospital of TCM, Shanxi Provincial Hospital of TCM, Shenzhen Baoan Hospital of TCM (Group), Xiamen Hospital of TCM, Jiangsu Provincial Hospital of TCM, and the First Affiliated Hospital of the Hunan University of TCM. A 12-week treatment phase plus a 12-week follow-up period make up the 24-week duration of this research. If they are qualified for the study, each participant is required to keep a diet and exercise diary for the whole research cycle. All participants will receive 12 weeks of individual treatments in two groups: the “moxibustion for harmonization of Yin and Yang” will be administered once every 1 week, 60 minutes each time; the gentle moxibustion will be administered 3 times a week, 20 minutes each time. Outcomes will be assessed at the beginning, at the conclusion, and during the follow-up period. The Standard Protocol Items: Recommendations for Intervention Trials (SPIRIT) [26] are utilized in the protocol, which is based on the Standards for Reporting Interventions in Clinical Trials of Acupuncture (STRICTA) [27](Additional file 1).  Figure 1 provides a summary of the trial's design.

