### 2.9. Sample Size

Based on an examination of the available research, clinical knowledge, and consultation with clinical professionals, the mean improvement of the waist circumference was 6.15 ± 1.56 cm ($\bar{x}\pm S$) in the “moxibustion for harmonization of Yin and Yang” group and 3.94 ± 1.14 cm ($\bar{x}\pm S$) in the gentle moxibustion group. A total of 96 individuals are needed in each group to achieve a one-sided significance level of *α* = 0.025 and an 80% power. A total of 216 patients will be included in the study, with 108 individuals per treatment arm, assuming a 10% dropout rate.

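### The economic comparison of two active regimens is expressed only as C/E, which does not give the extra cost of the extra effect and can misrank the arms

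*Protocol article*

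**What the plan says.** Section 2.1 lists, as part of objective 2, to "compare the safety, efficacy, and health economic evaluation of different moxibustion methods for treating menopausal obesity", with the aim of arriving at a better prescription. The Introduction repeats that the economic evaluation, like safety and efficacy, sets the harmonization regimen against the other arm: "compared to the gentle moxibustion, in order to increase the therapeutic impact".

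The method is one sentence at the end of section 2.8.2: "Health economics evaluation adopts cost-effective analysis, expressed in cost-effectiveness", followed in brackets by cost over effectiveness and the symbol C/E. Section 2.11 (Statistical Analysis) does not mention economics. Nowhere does the article refer to a difference in cost between arms, an incremental ratio, net benefit or a value per unit of effect. It gives no costs and does not say which outcome serves as E.

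Three other statements bear on the point:
- Section 2.9 gives the expected effects: "the mean improvement of the waist circumference was 6.15 ± 1.56 cm" in the harmonization arm and 3.94 ± 1.14 cm in the gentle arm.
- Section 2.2 gives the schedules: harmonization "will be administered once every 1 week, 60 minutes each time", and "the gentle moxibustion will be administered 3 times a week, 20 minutes each time".
- Section 2.7.1 gives both arms the same lifestyle programme through treatment and follow-up.

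**The concern.** The decision behind objective 2 is which of two regimens to prefer. That needs the additional cost of moving from one to the other and the additional effect obtained for it. A ratio formed within each arm instead sets that arm against an option with no cost and no effect, which is not in this trial. The effect in each arm also contains whatever the shared lifestyle programme achieves, and with no lifestyle-only arm that part cannot be separated out.

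C/E is therefore a named statistic that does not fit its stated purpose, which is different from a detail left to a fuller document. What is at stake is the economic conclusion on a secondary outcome: a comparison of two C/E values could point to one regimen when the incremental figures point to the other.

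**Working it through.** The article states no economic figure, so there is none to reproduce. The check compares the two summary measures on the article's own expected effects.

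**Inputs**
- Effects (section 2.9): E1 = 6.15 cm (harmonization), E0 = 3.94 cm (gentle). Difference: 6.15 − 3.94 = 2.21 cm.
- Assumption: E is waist reduction in cm. It is the primary outcome and the natural reading, but section 2.8.2 does not say so.
- Assumption: gentle-arm cost C0 = 100 units, harmonization cost C1 varied.

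**Formulas**
- C/E per arm: C1/E1 and C0/E0.
- Incremental ratio: (C1 − C0)/(E1 − E0).
- Net benefit at value λ per cm: λE − C. Harmonization is ahead of gentle when λ × 2.21 > C1 − C0.

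**Where the C/E ranking flips.** C1/E1 = C0/E0 when C1/C0 = E1/E0 = 6.15/3.94 = 1.56. Below that cost ratio C/E favours harmonization, and above it gentle. λ does not enter.

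**Results**

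| C1 | C1/6.15 | 100/3.94 | C/E favours | (C1 − 100)/2.21 | Net benefit disagrees if |
|---|---|---|---|---|---|
| 80 | 13.0 | 25.4 | harmonization | dominant (cheaper and better) | never |
| 130 | 21.1 | 25.4 | harmonization | 30/2.21 = 13.6 | λ < 13.6 |
| 200 | 32.5 | 25.4 | gentle | 100/2.21 = 45.2 | λ > 45.2 |

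**Check of the reversals with a value of λ filled in**
- C1 = 200, λ = 50: harmonization 50 × 6.15 − 200 = 107.5; gentle 50 × 3.94 − 100 = 97.0. Harmonization is ahead although its C/E is higher.
- C1 = 130, λ = 10: harmonization 10 × 6.15 − 130 = −68.5; gentle 10 × 3.94 − 100 = −60.6. Gentle is ahead although its C/E is higher. Both values are negative here, so this reversal concerns only the choice between the two arms.

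**Effect of the shared lifestyle programme.** Assume it contributes the same s cm to each arm, additively, and that only the remainder is credited to moxibustion. The C/E flip point becomes (6.15 − s)/(3.94 − s):
- s = 0: 1.56
- s = 1: 5.15/2.94 = 1.75
- s = 2: 4.15/1.94 = 2.14
- s = 3: 3.15/0.94 = 3.35

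At a cost ratio of 2, C/E favours gentle for s = 0 or 1 and harmonization for s = 2 or 3. The incremental denominator stays at 2.21 throughout.

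**The case against.** The strongest reply is that a journal article gave economics one sentence, that averaging per arm is a reading of C/E, and that a full protocol or economic plan may add an incremental analysis. It is true that such a plan could exist, and bootstrap details, cost items and perspective can properly be left to it. But the article does not leave the measure open. It names C/E, and cost over effect is that symbol's plain meaning.

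A second reply is that the ranking may turn out the same. This stands in part. Harmonization has 12 sessions against 36, with equal total time (12 × 60 = 36 × 20 = 720 minutes), but it uses more material per session (section 2.7.2). The direction of the cost difference is unknown. If harmonization proves both cheaper and better, C/E and the incremental analysis agree.

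Third, the consequence is limited. This is the last-listed secondary outcome, and the Discussion's own list of secondary outcomes leaves it out. That is correct, and it bears on the weight of the point, not on its substance.

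A reader might infer two stronger things that the text does not support:
- That the trial will declare the arm with the lower C/E the more cost-effective. No section states such a ranking rule.
- That C/E will be computed patient by patient, and so be undefined or negative when a waist does not shrink. Nothing says the ratio is formed per patient, and with arm means such as 6.15 and 3.94 cm the problem does not arise.

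**Conclusion.** The point holds in a limited form. C/E is the only economic measure the article states, and it does not answer the comparative question in objective 2. Used to compare the arms, it can rank them wrongly in either direction unless one arm is both cheaper and better. Whether it would do so in this trial cannot be said, because no costs are given.

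The flip at a cost ratio of 1.56 rests on the protocol's expected effects and on taking E as waist reduction. The thresholds of 45.2 and 13.6 per cm also rest on the assumed costs. The mismatch between a within-arm ratio and a between-arm decision does not depend on which outcome is chosen as E. The change should be made, but the primary analysis, the sample size and participant safety are not affected.

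**What to change.** In section 2.8.2, state that the economic comparison between arms will be incremental. Report:
- the difference in mean cost;
- the difference in mean effect for one named outcome and week, for example waist reduction at week 12, the end of treatment (section 2.8.1 lists several weeks and marks none as primary, so the week has to be named);
- their ratio, or net benefit over a range of values per cm, with a bootstrap interval;
- dominance, stated explicitly, where one arm is both cheaper and better.

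C/E per arm may stay as description.

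The cost is a sentence or two of text and a little more analysis on the costs that C/E already requires, with no additional patients or visits. The bootstrap interval needs costs held per patient. The article does not describe cost collection, so this should be confirmed. If a fuller plan already specifies an incremental analysis, the article only needs to be aligned with it.

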### 2.9. Sample Size

Based on an examination of the available research, clinical knowledge, and consultation with clinical professionals, the mean improvement of the waist circumference was 6.15 ± 1.56 cm ($\bar{x}\pm S$) in the “moxibustion for harmonization of Yin and Yang” group and 3.94 ± 1.14 cm ($\bar{x}\pm S$) in the gentle moxibustion group. A total of 96 individuals are needed in each group to achieve a one-sided significance level of *α* = 0.025 and an 80% power. A total of 216 patients will be included in the study, with 108 individuals per treatment arm, assuming a 10% dropout rate.

### 2.10. Data Monitoring and Management

Print and digital case report forms will be used to maintain all data (CRFs). Primary entries cannot be modified, and any corrections require a signature in the appended comments along with an explanation. CRFs are only accessible to outcome assessors, and duplicate data input will be done. All facets of the company are under the control of the Wuhan research team. Every month, this experiment and its results will be monitored by the Hubei Provincial Hospital of TCM's ethics committee, which will also ultimately decide whether to end the trial. Interventionists will keep an eye out for negative situations and respond properly with advice and encouragement. The protocol requirements must be understood and followed by all researchers, acupuncturists, and related personnel.

### 2.11. Statistical Analysis

SAS 9.3 software will be used by an impartial statistician to analyze the data (SAS Institute Inc, Cary, NC). Any participant who completes the randomized stage and receives at least one intervention will be analyzed using a full analysis set (FAS), with missing data for the important outcomes interpolated with the last observation carried forward, in accordance with the intention-to-treat (ITT) analysis strategy. Multiple imputations will be used to deal with missing data. All statistical inspections were used for bilateral testing, and statistical significance will be determined at *P* < 0.05.

For the patient's missing data, it is assumed that the deletion data is randomly missing, the lacking value of the research main indicator is used for multiple filling methods, the stochastic missing deletion assumption of multiple filling is performed, and the stability test of the missing data filling results is carried out by using pattern mixture model (PMM). The measurement data is described by average ± standard deviation ($\bar{x}\pm S$), median, maximum, and minimum, and the counting data and grade data are described by cases and percentages. Intergroup comparison will select the analysis method according to the data distribution feature: the measurement data is used to test or nonparameter testing; the count data is used in*χ*^2^inspection or Fisher's exact probability method, and the grade data is used in the nonparameter test. Compared with the baseline value, the metering data is used in pair*T*inspection or nonparameter test, and counting materials use nonparameter test.

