#### 2.4.3. Withdrawal from the Study

Pregnancy or other diseases are found during treatment, or serious adverse reactions and complications occur, and a specialist physician at each center decides to terminate the patient's participation in the trialCombines the treatment methods prohibited by this study or changes the specified treatment method halfwayPoor compliance and unable to implement treatment in accordance with the prescribed test protocolParticipant's decision to withdraw from the study

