### 2.13. Quality Control

The acupuncture, methodology, and statistics specialists examine and make revisions to the study protocol. A predetermined standard operating procedure will be used to teach the relevant employees. Through health education and prompt follow-up, patient compliance will be increased. If the subjects stop using moxibustion or depart from the procedure, the results will also be assessed by outcome assessors. This study will carry out a central randomization system to prevent bias in selection. At the same time, one of the most crucial strategies for preventing bias is the careful selection of inclusion and exclusion criteria, contributing to the objectivity of conclusions. A third-party blinded method will be applied to this study, namely, for assessing efficacy and safety by assessors who are not familiar with the group characteristics. To ensure the smooth progress of the study, all clinical researchers will be trained in the SOPs about moxibustion before the study begins to improve the consistency of researchers' and spectators' internal observations, in order to guarantee the validity of the conclusions. We will conduct sensitivity analyses in the per-protocol set. During this study, we will hold regular multicenter team meetings and go through routine checks to prevent center bias.

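### Section 2.11 gives waist circumference two incompatible missing-data rules, LOCF and multiple imputation, and makes neither primary

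*Protocol article*

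**What the plan says.** All the missing-data rules stand in Section 2.11 (Statistical Analysis).

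- The analysis set is defined first: "Any participant who completes the randomized stage and receives at least one intervention will be analyzed using a full analysis set (FAS").
- The same sentence attaches LOCF to that analysis: "with missing data for the important outcomes interpolated with the last observation carried forward, in accordance with the intention-to-treat (ITT) analysis strategy".
- The next sentence is unrestricted: "Multiple imputations will be used to deal with missing data".
- The second paragraph states the assumption, "it is assumed that the deletion data is randomly missing", and applies multiple imputation to the primary outcome: "the lacking value of the research main indicator is used for multiple filling methods".
- It then names a robustness check: "the stability test of the missing data filling results is carried out by using pattern mixture model (PMM").

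Section 2.8.1 makes waist circumference the only primary outcome, measured at weeks 0, 4, 8, 12, 18 and 24. Section 2.13 adds a per-protocol sensitivity analysis.

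Two related statements lie elsewhere. Section 2.4.3 lists among the grounds for leaving the study a changed treatment method and poor "compliance and unable to implement treatment in accordance with the prescribed test" protocol. Section 2.13 says: "If the subjects stop using moxibustion or depart from the procedure, the results will also be assessed by outcome assessors". The Abstract promises an intention-to-treat analysis that includes participants who withdraw.

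**The concern.** The important outcomes of the first rule must include the only primary outcome, and the main indicator of the second rule is that outcome. Waist circumference is thus to be filled by LOCF and also by multiple imputation. The two methods rest on different assumptions and can give different estimates and standard errors. With no stated order between them, two analysts who each follow the plan could report different primary results, and the choice could be made after unblinding.

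The two rules are also not equally sound here. The plan assumes MAR. Under that assumption LOCF is biased when waist keeps changing after the last visit, and repeated visits during a 12-week treatment phase are scheduled because change is expected. LOCF also counts each filled value as a real observation, so uncertainty is understated. Dropout could differ between arms, because one attends once a week and the other three times a week (Section 2.2). The LOCF error would then not cancel.

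**Working it through.** The plan gives no figure for the effect of missing data, so there is none to reproduce. The calculation below illustrates how far LOCF can depart from the MAR target.

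**Inputs from the document.** Section 2.9 gives mean waist improvements of 6.15 cm (harmonization) and 3.94 cm (gentle), a difference of 6.15 - 3.94 = 2.21 cm. It also gives an overall dropout rate of 10%. Section 2.2 gives 108 per arm.

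**Assumptions not in the document.** The two means are reached at week 12, waist falls linearly from week 0 to week 12, and dropout does not depend on outcome. The split of dropout between arms and the last visit attended are varied.

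**Formula.** Let c be the share of the week-12 loss reached at the last visit: c = 0, 1/3 or 2/3 for week 0, 4 or 8. LOCF understates each dropout's loss by (1 - c) times the arm mean. For dropout shares p1 (harmonization) and p2 (gentle):

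bias = -p1 × 6.15 × (1 - c) + p2 × 3.94 × (1 - c)

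**Last visit at week 4.** The shortfalls are 6.15 × 2/3 = 4.10 cm and 3.94 × 2/3 = 2.63 cm.

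- 10%/10%: -0.410 + 0.263 = -0.147 cm, and 0.147/2.21 = 6.7%
- 15%/5%: -0.615 + 0.131 = -0.484 cm, 21.9%
- 5%/15%: -0.205 + 0.394 = +0.189 cm, 8.6%

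**Range over the last visit (bias in cm, % of 2.21).**

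| Dropout harmonization/gentle | Week 0 | Week 4 | Week 8 |
|---|---|---|---|
| 10%/10% | -0.22 (-10.0%) | -0.15 (-6.7%) | -0.07 (-3.3%) |
| 15%/5% | -0.73 (-32.8%) | -0.48 (-21.9%) | -0.24 (-10.9%) |
| 5%/15% | +0.28 (+12.8%) | +0.19 (+8.6%) | +0.09 (+4.3%) |

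Under these assumptions, correctly specified multiple imputation under MAR targets 2.21 cm in every cell.

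**No true difference.** A simulation gave both arms the same mean loss, (6.15 + 3.94)/2 = 5.045 cm, with SD sqrt((1.56² + 1.14²)/2) = 1.366 cm and 108 per arm. The last visit of each dropout was drawn at random from weeks 0, 4 and 8. Over 4,000 runs of a two-sided 5% Welch t-test, LOCF rejected in 5.2% of runs at 10%/10% dropout, 30.3% at 5%/15% and 29.6% at 15%/5%. Equal dropout leaves the type I error intact; unequal dropout does not.

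**The case against.** The strongest reply is that the intention can be guessed. For the main outcome, Section 2.11 sets out a coherent package of MAR, multiple imputation and a pattern-mixture check, while LOCF has one clause. This supports the repair below, but it does not remove the contradiction. The LOCF clause is attached to the intention-to-treat analysis itself, and nothing confines it to secondary outcomes or to a sensitivity role. A separate analysis plan could choose one rule, but the protocol text would still state both.

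The reply on size is stronger, and most of it stands. The document gives only a 10% overall dropout rate. It does not say that the planning means are week-12 values, and Section 2.8.1 fixes no primary time point. The biases of -0.48 and +0.19 cm, and the type I error near 30%, need an assumed threefold imbalance. The shortfalls also suppose that a patient who leaves at week 4 would have gone on to the full-treatment mean. If the target is the outcome whether or not treatment continued, such a patient might lose less. The LOCF shortfall would then be smaller, and imputation built on those who continued could overstate the loss.

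A reader might also infer that the article itself predicts regain of weight after treatment, which would make carrying week 12 forward to week 24 plainly wrong. It does not. The rebound remark in the Introduction describes diet and exercise as a competing approach, not the course after moxibustion, and Section 2.7.1 continues the lifestyle programme through follow-up.

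On the analysis set, requiring at least one treatment is a common modified intention-to-treat definition. The fault is mainly the label, and the number of patients affected cannot be computed. On withdrawal, Section 2.13 and the Abstract already point towards continued assessment and inclusion, so it would be too strong to say that the plan simply removes non-compliers.

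**Conclusion.** The point holds as a contradiction within Section 2.11: two missing-data rules apply to the same primary outcome and neither is made primary. This does not depend on any calculation.

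Under the plan's MAR assumption, LOCF is the biased rule if waist keeps changing after dropout. With linear loss to the Section 2.9 means by week 12 and a last visit at week 4, the bias is about -0.15 cm, 7% of 2.21 cm and conservative, when the stated 10% dropout falls equally. It is -0.48 or +0.19 cm under the assumed 15%/5% and 5%/15% splits. A reader might infer that the trial faces a 22% bias or an inflated type I error. The document does not support this, because both need unequal dropout that it nowhere states. Nor does it follow that two analysts would necessarily disagree; they could.

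Two minor wording faults go with it. A set that excludes randomised patients who had no session is labelled intention-to-treat. Sections 2.4.3 and 2.13 differ on whether patients who comply poorly or change treatment are still assessed.

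**What to change.** 1. In Section 2.11, delete the LOCF clause or label it explicitly as a sensitivity analysis.
2. Name multiple imputation under MAR as the single primary method for waist circumference, using the waist values already scheduled at earlier visits. Keep the pattern-mixture model as the sensitivity analysis. Offering a second primary method as an alternative would recreate the defect.
3. Either call the set that requires at least one intervention modified intention-to-treat, or analyse all randomised participants, as the Abstract's statement implies.
4. Reconcile Section 2.4.3 with Section 2.13 as regards outcome collection, so that it is clear whose outcomes are still recorded after poor compliance or a change of treatment. The physician-decided terminations in Section 2.4.3 are a clinical matter and are not questioned here.

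The cost is wording in the protocol, and in the analysis plan if there is one. No visits or measurements are added. If all randomised participants are analysed, any patients who were never treated would add some imputed values.
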